### Blinding

Participants and outcome assessors will be blinded to the treatment group allocations. It is not possible to blind the physician; therefore, the Korean medicine doctor (KMD) who will perform the treatment will not participate in the trial outcome assessment or data collection and analysis.

Each hospital will designate several KMD trained to perform the therapy and obtain relevant operational qualifications.

The outcomes will be assessed before and after the intervention. To ensure blinding, we will choose a sham device as a placebo control in this participant-assessor-blinded clinical trial and use eye masks to shield the participants’ eyes.

The treatment device will be of the same size and material, and the treatment method will maintain a consistent frequency and intensity.

In case of serious AEs, the principal investigators at each participating center will decide whether allocation concealment needs to be broken. If allocation concealment is broken before the end of the trial, the data will be censored from the analysis and the patients will be considered to have dropped out of the trial.

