### Safety evaluation

Several safety measures will be undertaken, including the observation of vital signs, blood test results, drug combination, physical examination, AEs, and severe AEs outcomes. The timeline for the safety evaluation is presented in Fig. 2. If an AE occurs, researchers must quickly attend to it and record the date of occurrence, severity, duration, and treatment measures. In the case of a serious AE, the researchers must take immediate action to ensure the safety of the participants, report it to the principal investigators and the Ethics Committee within 24 h, and determine if the participant should be withdrawn based on the condition.

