#### General principles

The safety and full analysis sets (FAS) of this trial will include all the participants who received any intervention at least once after randomization. The per-protocol set will only include participants in the FAS who completed the entire trial without protocol violations. The FAS is primarily used for outcome analysis, although additional outcome analyses of the per-protocol set may be performed. The safety set will be used for safety assessments, including the primary outcome of the trial. Missing values will be handled using the last observation carried-forward method.

Statistical analyses will be performed using SAS (SAS Institute Inc., Cary, NC, USA) or SPSS (IBM Corp., Armonk, NY, USA) softwares for Windows. Statistical significance is set at *p* < 0.025 for a one-tailed test and *p* < 0.05 for a two-tailed test.

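### The rule that censors a participant's data after a code break, for which a serious AE is the only named trigger, conflicts with the definitions of the FAS and the safety set

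*Protocol article*

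**What the plan says.** The Blinding section of the protocol article names one situation in which the code may be broken: "In case of serious AEs, the principal investigators at each participating center will decide whether allocation concealment needs to be broken". The next sentence gives the consequence: "If allocation concealment is broken before the end of the trial, the data will be censored from the analysis". It adds that "the patients will be considered to have dropped out of the trial".

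General principles, under Statistical analysis, defines the analysis sets: "The safety and full analysis sets (FAS) of this trial will include all the participants who received any intervention at least once after randomization". On their use it says "The safety set will be used for safety assessments" and "The FAS is primarily used for outcome analysis". On missing data it says "Missing values will be handled using the last observation carried-forward method". None of these sentences makes an exception for a participant whose code was broken.

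Safety evaluation lists, among its measures, "physical examination, AEs, and severe AEs outcomes". Economic outcomes analysis works primarily on all randomised participants.

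**The concern.** A treated participant whose code is broken belongs to the FAS and the safety set under General principles, yet under Blinding that participant's data leave the analysis. Taken at face value, both rules cannot be followed.

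The conflict matters because of what triggers it. Inclusion in the analysis comes to depend on an event after randomisation (a serious AE) and on a local, case-by-case decision that follows it. That event is one of the things the safety analysis exists to count. Safety is a stated aim of the trial, and the Discussion wants the result to support broader coverage of the device. A safety table that omits some serious AEs by rule would weaken that evidence, whichever arm they came from.

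**Working it through.** **1. The texts side by side**

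| Question | Blinding | General principles |
|---|---|---|
| Is a treated, unblinded participant analysed? | Data censored from the analysis; patient is a dropout | In the FAS and the safety set |
| Is there a limit to efficacy data? | None stated | Not applicable |
| Is there a limit to data after the break? | None stated | Not applicable |
| Is there an exception for a code break? | This is the rule itself | None stated |

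**2. Two readings of the word *censored***

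- *Exclusion.* All data of the participant leave the analysis. This contradicts both set definitions, and the triggering serious AE is not tabulated.
- *Cut-off at the break.* Data up to the break stay. The triggering event is counted, because it comes first. Safety data after the break, including the further course of that event, are still lost, and missing efficacy values fall to LOCF.

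The sentence gives no time point and speaks of the data without qualification, so exclusion is the more natural reading. Neither reading keeps all the safety data of a treated participant.

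**3. Size for the safety result (assumed counts)**

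The document gives no serious AE rate, so every event count below is an assumption. The denominator is the planned 92 per group, which reproduces from Sample size: 64 / (1 − 0.30) = 91.4, rounded up to 92.

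Suppose k participants in one arm have a serious AE, all are unblinded and all are excluded. The true rate is k/92 and the reported rate is 0/(92 − k). With zero events, the upper limit of the two-sided 95% interval is 1 − 0.025^(1/(92 − k)).

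| k | True rate | Reported | Upper limit as reported |
|---|---|---|---|
| 1 | 1/92 = 1.1% | 0/91 | 4.0% |
| 2 | 2/92 = 2.2% | 0/90 | 4.0% |
| 3 | 3/92 = 3.3% | 0/89 | 4.1% |
| 5 | 5/92 = 5.4% | 0/87 | 4.2% |

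For k = 3 the exact (Clopper–Pearson) 95% interval without exclusion is 0.7% to 9.2%. For k = 5 the upper limit after exclusion lies below the rate that occurred.

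Unblinding is discretionary. If only 1 of 3 such participants is unblinded, the report shows 2/91 = 2.2% instead of 3/92 = 3.3%. This is understated, but not zero.

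**4. Direction**

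Take k = 3, all unblinded and excluded:

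- All in the BMA arm: a true difference (BMA minus sham) of +3.3 percentage points is reported as 0, which favours the device.
- All in the sham arm: a true difference of −3.3 points is reported as 0, which works against the device.
- Three in each arm: the difference stays 0, but the overall rate falls from 6/184 = 3.3% to 0/178.

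**5. Size for the efficacy result**

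If the k excluded participants have mean change m and the whole arm has mean M, exclusion shifts the arm mean by k(M − m)/(92 − k). Take M = 9.2, the 4-week O-SCORAD change in the BMA group of the earlier study (Sample size), and assume no improvement in the excluded (m = 0). For k = 3 the shift is 3 × 9.2 / 89 = 0.31 points. The two groups of that study differed by 9.2 − 7.2 = 2.0 points. The effect on efficacy is therefore small unless many codes are broken.

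**The case against.** The best defence is the cut-off reading. The sentence says *censored* and *dropped out*, not excluded, and names neither the FAS nor the safety set. A treated dropout still meets both set definitions, and LOCF would supply the missing efficacy values. This reading is possible and would keep the triggering event in the tables. It is not what the sentence most naturally says, and it still discards safety data after the break.

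Safety evaluation also requires AEs to be recorded, and serious AEs to be reported within 24 hours to the principal investigators and the Ethics Committee. So the events are not lost from the trial's records. That governs recording and reporting, however, and does not put an event back into a comparative analysis from which its data were censored.

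The article mentions a statistical analysis plan that is not shown, and it may handle code breaks in detail. But the point is a rule that the article states, not a gap. The plan could only choose one side of the conflict.

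A reader might go further and infer that the rule removes the worst safety cases, or that it biases the trial in favour of the device. The document supports neither. Unblinding is optional, so only some serious AEs are touched, and nothing says those are the gravest. The rule applies to both arms, so its direction depends on where the events fall. Nor does the document support any particular event count: it reports no adverse events in the BMA group of the exploratory study (n = 30), which is too small to exclude a risk and gives no rate to plan on.

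**Conclusion.** The conflict is real and stands in the current text. Read literally, Blinding takes out of both the safety and the efficacy analysis those participants whose serious AE led to unblinding, while General principles keeps them in both. The exclusion depends on a post-randomisation event and can understate serious AEs in either arm. It would favour the device only if such events occurred mainly in the BMA arm.

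The number affected is unknown and probably small, and the effect on the primary efficacy comparison should be slight. The safety result is more exposed, because with rare events even one to five exclusions can turn an observed rate into zero. The figures above rest on assumed event counts, on full unblinding except where stated, and on the exclusion reading.

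They also take a code break to mean unblinding after a serious AE. Randomization and allocation has the investigators tell participants their assignment at enrolment, which conflicts with participant blinding. That is a separate matter.

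**What to change.** Replace the censoring sentence in Blinding with a statement that:

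- a code break does not change membership of the FAS or the safety set;
- all AE data, before and after the break, are kept in the safety analysis;
- efficacy data that are collected stay in the FAS analysis;
- the date of the break and the reason for it are recorded.

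Confine any exclusion of unblinded participants, or of their efficacy data after the break, to the per-protocol set or a sensitivity analysis. Unblinding need not be called a protocol deviation, since the protocol itself permits it after a serious AE. The SAP should carry the same wording.

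The cost is a short replacement text and, if wanted, one extra sensitivity analysis. The change concerns analysis only and leaves the decisions to unblind or to stop treatment as they are. The downside is that a few patient-reported scores (POEM, DLQI, pruritus VAS) taken after unblinding may be affected by knowledge of allocation. The sensitivity analysis without those data addresses this.

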### Study timeline

The study protocol comprises two main phases over 7 weeks: the screening and treatment phases (Fig. 1). The screening period will last 2 weeks, and participants will be included in this phase according to the inclusion/exclusion criteria. Participants will be treated three times a week for 4 weeks, with different interventions among the groups.

#### Screening phase 

Participants will be enrolled in the screening phase and physical examinations and inclusion evaluations will be performed. The trial’s eligible participants will be requested to complete a written informed consent form (including the procedures, risks, and options for quitting the study). The study will be thoroughly explained to the participants by a researcher with the required training. Participants will sign an informed consent form upon providing approval.

#### Treatment phase

The participants will receive interventions during the treatment phase. Participants will be checked for the O-SCORAD index, visual analog scale (VAS), Eczema Area and Severity Index (EASI), Dermatology Life Quality Index (DLQI), Patient-Oriented Eczema Measure (POEM), AEs, and compliance during the 4-week therapy period, administered three times a week.

After 5 weeks, all the interventions will be terminated. We will assess the demographic characteristics, medical and medication histories, skin lesion images, personal life histories, vital signs, physical examinations, and AEs (Fig. 2).

**Fig. 2 Fig2:**
[figure not shown]
Study timeline and assessment schedule this figure presents the timeline of the study, detailing the significant phases from participant enrollment to study conclusion. It encompasses screening, randomization, intervention, and follow-up assessments over a duration of 8 weeks. Key milestones within the study include participant education, eligibility assessment, the administration of interventions (BMA or sham BMA), and clinical evaluations, all scheduled at specific intervals. The outcome assessments comprise vital signs, blood tests, SCORAD index, VAS, POEM, EASI, DLQI, collection of gut microbiome samples, monitoring of adverse events, and economic evaluations. This organized timeline facilitates the thorough monitoring of participants and the systematic collection of data throughout the trial. S/I: Sociodemographic information; P/E: Physical examination; C/P: Clinical pathology test; P/H: Past history; M/H: Medication history; T/H: Treatment history; BMA: Biodegradable microneedle acupuncture; Sham BMA: Sham Biodegradable microneedle acupuncture; O-SCORAD: Objective-SCORing Atopic Dermatitis. VAS: Visual analog scale; POEM: Patient-oriented Eczema Measure; EASI: Eczema Area and Severity Index; BT/AT discomfort: Discomfort before and after treatment; MDRT diary: Medical Device Removal Time record diary; RM : Rescue medication

### Intervention

#### BMA / sham device treatment

The experimental group will receive treatment with BMA (RMD-PN1, Raphas Co. Ltd., Seoul, Republic of Korea), whereas the control group will receive sham BMA treatment (Fig. 3).

**Fig. 3 Fig3:**
[figure not shown]
Comparison of sham and biodegradable microneedle acupuncture (BMA) Patches This figure illustrates the sham and BMA patches utilized in the research. The upper section depicts the external packaging of both patches, which are designed to be indistinguishable to maintain blinding. The central section reveals the internal product, featuring a circular patch with a clear protective layer. The lower section emphasizes a significant distinction: the sham patch is devoid of microneedles, whereas the BMA patch is equipped with biodegradable microneedles on its surface

All the treatments will be administered by a KMD with more than 1 year of clinical experience in Korean medicine dermatology. The KMD will have undergone more than 10 h of training and simulation to ensure that they are able to provide identical acupuncture treatment in accordance with the predefined protocol.

A total of 184 participants with indications for the 10 acupoints (PC6, LI4, LI11, ST36, and SP10, bilaterally) (Fig. 4) will be randomly assigned to the BMA or sham device treatment groups in a 1:1 ratio. The assigned participants will be treated with BMA or a sham device.

**Fig. 4 Fig4:**
[figure not shown]
Locations of acupoints for biodegradable microneedle acupuncture (BMA) Treatment This figure depicts the five acupoints utilized in the study for BMA treatment. The chosen acupoints are LI11 (Quchi), LI4 (Hegu), PC6 (Neiguan), ST36 (Zusanli), and SP10 (Xuehai). These points are strategically positioned on the arms and legs and are frequently employed in traditional Korean medicine to manage inflammation, modulate the immune system, and treat skin-related issues. The application of BMA at these specific points is intended to amplify the therapeutic effects for symptoms associated with atopic dermatitis (AD)

For 4 weeks, treatments will be performed three times a week for a total of 12 times.

The investigators will instruct the participants on how to remove the BMA and disinfect the treated area themselves 4 h after treatment. The investigators will distribute Medical Device Removal Time record diaries to the participants at each visit and instruct them on the removal time record sheets.

### Participant daily life management training

Throughout the trial, all patients will receive standard basic daily life management (health guidelines) as follows.

Skin moisturizing and carei.Apply moisturizer frequently to prevent your skin from drying out. After bathing, gently pat your skin dry and apply moisturizer within 3 minutes.ii.Use a mild, neutral soap when bathing, and rinse out the soap thoroughly.iii.Avoid saunas, as they can exacerbate skin itch even more.iv.Bath water should be tepid, and avoid scrubbing as it can irritate the skin and exacerbate AD.v.Skin infections can exacerbate AD; therefore, it is essential to keep the skin and any wounds clean.vi.Stress can exacerbate AD by causing you to scratch your skin; therefore, it is important to relax and keep your fingernails trimmed.Wear soft cotton clothingi.Avoid clothing made from synthetic fibers, such as coarse wool, nylon, and other non-cotton fabrics.ii.After washing, rinse well to remove any detergent from your clothes.iii.Maintain an appropriate room temperature and humidity level.Maintain a temperature and humidity level that makes you feel comfortable, as sweaty conditions, such as hot rooms, heavy blankets, or clothing and high fever can exacerbate AD.The optimal temperature is 22–24℃ and the optimal humidity level is 40–50%.Avoid allergy triggersi.If you are allergic to dust mites, pollen, or animal hair, consider avoiding pets and carpets.ii.Avoid allergens through the air, such as formaldehyde—can cause sick building syndrome— and air pollutants.Avoid irritating and allergenic foodsi.Avoid spicy, salty, irritating, fatty, and instant foods.ii.Food such as milk, eggs, flour, nuts, seafood, food additives, and preservatives should be avoided.

### Rescue medication

Participants with severe pruritus may be allowed to apply Lidomex cream 0.15% (prednisolone valeroacetate) as a rescue medication in consultation with the investigators. In this case, investigators teach to apply the rescue medication with the fingertip unit method and record the use of the rescue medication at every visit.

### Combination treatment

#### Combination treatments permitted

Patients with co-morbidities or newly developed co-morbidities will be allowed to take specific medications or other treatments during the study, but only if the details are included in the medical record for analysis.

Concomitant medications and treatments that the participant has been taking prior to entering this study that the investigator believes will not affect the interpretation of the results and will be allowed at the discretion of the investigator.

#### Combination treatment prohibited

Systemic corticosteroidsImmunosuppressantsAny other drug or dietary supplement not recognized by the principal investigator.Concomitant treatment of any kind (including herbal treatments) related to AD is prohibited, with the exception of the rescue medication.

### Outcome measures

#### Primary outcome measure

An independent researcher will evaluate the outcomes. The schedules are listed in Fig. 2. The primary measurable outcome is the change in the O-SCORAD before (baseline) and after (5 weeks) treatment. O-SCORAD scores are designed to be measured at the screening phase, Visit 1, and Visit 13.

The O-SCORAD excludes subjective symptoms of itching and sleep disturbance from the total SCORAD [10]. A score of 15 to 40 is moderate and 1 to less than 15 is mild.

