### Eligibility criteria

#### Inclusion criteria

Patients meeting all the following criteria will be enrolled in this study:

Male or female patients aged 19–70 years at the screening visit.Diagnosis of AD according to the Hanifin and Rajka criteria (> 3 of 4 major symptoms and > 3 of 23 minor symptoms).Patients scored 10–40 in the O-SCORAD index.Patients who can read and write Korean and who voluntarily submitted written consent with their signature.

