### Sample size

In our previous study, the mean changes in the O-SCORAD score for 4 weeks were 9.2 ± 3.73 and 7.2 ± 3.91 in the BMA-AD and IDA-AD groups, respectively. Based on these results, we will conservatively evaluate the changes for 4 weeks in the BMA and sham devices. The number of participants required for this study was calculated as follows:$${n}_{1}=\frac{{2({Z}_{\alpha/2}+{Z}_{\beta})}^{2}{\sigma}^{2}}{{\left(\mu1-{\mu}_{2}\right)}^{2}}=64$$

The required sample size was determined to be 64 cases per group (‘experimental group’ and ‘control group’).$$N=\frac{{n}_{1}}{1-r}\cong92$$

Assuming a 30% drop out rate of participants at follow-up, we calculated the sample size to be 92 cases for each group and a total of 184 participants for both groups.

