#### Primary and Secondary efficacy outcome analysis

The values of the efficacy outcomes will be presented as descriptive statistics. Differences in the values before and after the interventions will be compared using the paired t-test or Wilcoxon signed-rank test, and a 95% confidence interval will be calculated. The statistical significance of the differences between the experimental and control groups at each assessment point will be determined using a two-sample t-test or Mann–Whitney U test.

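### O-SCORAD is scored twice before treatment, but the stated between-group test takes no covariate, so the primary comparison does not fully use pre-treatment information already collected (lost precision, not bias)

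*Protocol article*

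**What the plan says.** The section Primary outcome measure sets the schedule: "O-SCORAD scores are designed to be measured at the screening phase, Visit 1, and Visit 13". It defines the endpoint as follows: "The primary measurable outcome is the change in the O-SCORAD before (baseline) and after (5 weeks) treatment". It does not say whether baseline means the screening score, the Visit 1 score or some combination. The secondary scales are scheduled only at Visit 1 and Visit 13, so only O-SCORAD has a second pre-treatment value.

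The screening score has a purpose of its own. Inclusion criteria require: "Patients scored 10–40 in the O-SCORAD index". Study timeline adds: "The screening period will last 2 weeks, and participants will be included in this phase according to the inclusion/exclusion criteria".

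The section Primary and Secondary efficacy outcome analysis fixes the between-group method: "The statistical significance of the differences between the experimental and control groups at each assessment point will be determined using a two-sample t-test or Mann–Whitney". The sentence before it, "Differences in the values before and after the interventions will be compared using the paired t-test" (or the Wilcoxon signed-rank test), describes the before-after comparison and not the randomised one. No covariate is named for either. Statistical analysis mentions a separate analysis plan, which is not shown.

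**The concern.** O-SCORAD is an assessor-rated score of a disease that fluctuates. A plain change score carries the rating error and short-term variation of its single baseline straight into the endpoint. A two-sample test on that change fixes the weight of the baseline at one and has no place for any other pre-treatment value. The trial schedules a second O-SCORAD before treatment, yet the stated comparison gives it no role.

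What is at stake is the precision of the BMA-versus-sham difference, in a trial planned on a difference of about half an SD (2.0/3.82 = 0.52) with 30% dropout allowed for. The validity of the randomised comparison is not at stake.

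**Working it through.** **Inputs from the protocol article.** Sample size: "the mean changes in the O-SCORAD score for 4 weeks were 9.2 ± 3.73 and 7.2 ± 3.91 in the BMA-AD and IDA-AD groups, respectively", so the difference is 9.2 − 7.2 = 2.0 and the pooled SD is √[(3.73² + 3.91²)/2] = 3.82. The same section gives 64 per group, 30% dropout and 92 per group. General principles: "Statistical significance is set at *p* < 0.025 for a one-tailed test and *p* < 0.05 for a two-tailed test"; two-sided 0.05 is used here.

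**Assumptions.** The article gives no correlations between O-SCORAD scores and no power. Correlations are varied below, with equal variances at the three time points. The two-sample test is read as applied to the change, the declared outcome.

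**The plan's own figure.** The printed formula at 80% power gives 2(1.960 + 0.842)² × 3.82²/2.0² = 57.3, so 58 per group, not 64. An SD of 4.0 gives 63 by that formula and 64 by the t-test. The dropout step reproduces: 64/0.70 = 91.4, so 92. The gap between 58 and 64 is a separate matter and does not affect what follows.

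**Power as stated.** With 64 per arm and SD 3.82 the noncentrality is 2.0/(3.82 × √(2/64)) = 2.96 on 126 degrees of freedom, which gives a power of 83.6%.

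**Variance formulas**, with the variance of one score set to 1. Let a = corr(screening, Visit 1), b = corr(Visit 1, Visit 13) and c = corr(screening, Visit 13).
- Change from Visit 1: 2(1 − b)
- ANCOVA on Visit 1: 1 − b²
- ANCOVA on both: 1 − (b² + c² − 2abc)/(1 − a²)
- Change from the mean of the two: 1 + (1 + a)/2 − b − c

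For power, the SD of 3.82 is multiplied by the square root of the variance relative to change from Visit 1.

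| a / b / c | Change | ANCOVA, Visit 1 | ANCOVA, both | Further cut from screening score | Power: change / Visit 1 / both |
|---|---|---|---|---|---|
| 0.5 / 0.5 / 0.5 | 1.000 | 0.750 | 0.667 | 11% | 83.6 / 92.4 / 94.9% |
| 0.6 / 0.6 / 0.6 | 0.800 | 0.640 | 0.550 | 14% | 83.6 / 90.7 / 94.3% |
| 0.7 / 0.7 / 0.7 | 0.600 | 0.510 | 0.424 | 17% | 83.6 / 89.0 / 93.8% |
| 0.7 / 0.6 / 0.5 | 0.800 | 0.640 | 0.627 | 2% | 83.6 / 90.7 / 91.3% |
| 0.8 / 0.7 / 0.6 | 0.600 | 0.510 | 0.506 | 1% | 83.6 / 89.0 / 89.3% |
| 0.8 / 0.7 / 0.5 | 0.600 | 0.510 | 0.500 | 2% | 83.6 / 89.0 / 89.6% |

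Worked example, fourth row: (0.36 + 0.25 − 2 × 0.7 × 0.6 × 0.5)/(1 − 0.49) = 0.19/0.51 = 0.373, and 1 − 0.373 = 0.627.

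**Averaging the two pre-treatment scores.** Relative to change from Visit 1, the variance ratio is 0.75 in the first three rows, then 0.94, 1.00 and 1.17. In the last row power falls to about 78%. Averaging gains only if a/2 + (b − c) < 0.5.

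**The case against.** The strongest reply is that nothing here is an error. Change from a single pre-treatment score is a conventional endpoint, the comparison is valid under any definition of baseline, and an unseen analysis plan may settle both the definition and the covariates. All of this stands as to severity. It does not remove the point, because the article does not leave the test open: it names two tests, and neither admits a covariate.

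Three stronger readings are tempting, and the documents do not support them.

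- A reader might infer that the screening score is thrown away. It is not: it decides the 10–40 entry criterion. That only O-SCORAD is scored at screening fits an eligibility check rather than a planned second baseline.
- A reader might infer that the plan commits to one of the two scores. Baseline is singular but undefined, so this is an inference.
- A reader might infer a sure 25% cut in variance, with power rising from 84% to 92%, from averaging the two scores. That needs the screening score to track Visit 13 as well as Visit 1 does. The screening period lasts 2 weeks, so decay over time is plausible, and averaging can then gain nothing or lose. Nor is it established that both scores were taken free of AD treatment: the exclusion criteria name systemic drugs in the month before screening and no topical washout, while AD-related treatment is prohibited during the trial.

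It is also fair to say that the screening score's own contribution may be small. In the decaying cases, moving to ANCOVA on Visit 1 supplies nearly all the gain.

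**Conclusion.** The point holds as a missed efficiency of low severity. The stated two-sample test leaves pre-treatment O-SCORAD information only partly used. At 64 per arm, adjusting for both scores takes power from about 84% to somewhere between 89% and 95%, given a difference of 2.0, an SD of change of 3.82 and assumed correlations of 0.5 to 0.8.

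Most of that range comes from adjustment as such. The share due to the screening score is 11% to 17% of residual variance under equal correlations of 0.5 to 0.7, and about 1% to 2% under decay. Every one of these figures rests on correlations that the article does not report. Both scores precede treatment, so using both cannot bias the randomised comparison, even though one of them also determined entry.

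**What to change.** In Primary outcome measure, name the Visit 1 O-SCORAD as the reference baseline. In Primary and Secondary efficacy outcome analysis, make the primary between-group analysis an ANCOVA of the Visit 13 O-SCORAD (or, equivalently for the treatment effect, its change from Visit 1), with the Visit 1 and screening scores as separate covariates so that the data set their weights. Do not define baseline as the mean of the two scores, since that can lose precision. Make the change before unblinding and carry it into the analysis plan.

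The cost is a line or two of wording and one more degree of freedom than adjusting for Visit 1 alone. No visit, assessment or participant is added. The screening score should be available for essentially everyone, because entry depends on it.
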